### Sample size justification and power analysis

The sampling scheme is stratified clustering with matched-pair sampling. Within each area, we pair matched clusters (villages) by distance to the HIV clinic and randomly assigned one village to be in the intervention arm. We have ensured that villages assigned to different study conditions are not within 4 km (1 h by foot) of each other to avoid possible discussions between different arms of participants.

We have powered the study to detect differences between the intervention and the standard-of-care for the primary outcome of HIV viral suppression (< 20 copies/ml) as well as intermediate outcomes: linkage to care and time to care, and, among those eligible for ART: time to and receipt of ART. Using census data, HBHCT acceptance rates from our own and other prior studies [22], HIV prevalence and prior knowledge of HIV status in this area from the recent prevalence survey [17], and estimating a 92% acceptance rate for enrollment of eligible participants into the study we calculated that the average cluster size (number of newly-diagnosed PLHIV per village who enroll in the study) will be 14 (range 8 to 37). In calculating the necessary clusters, type I error rate, desired power of tests, measure of effectiveness between the intervention and control group, cluster size, and coefficient of variation (k) or intraclass correlation coefficient are needed. We estimated viral suppression at 12-month follow-up among those eligible for ART at baseline to be 55% in the standard-of-care arm and 75% in the intervention arm. This estimate takes into account 12-month viral suppression success rates from SSA public sector ART programs [45, 81–84] and our own [23, 39] and others’ data on intermediate outcomes of linkage to care and ART initiation [22, 28]. With a type I error rate of 0.05 (two sided), average cluster size of 14, power of 80%, 12% difference in outcomes, and coefficient of variation of 0.24, we need 40 clusters after accounting for a 18% attrition rate for the follow-up. We expect that the 40 clusters will yield approximately 600 PLHIV participants across the two study arms.

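### The sample-size statement claims 80% power for a 12% difference, but 40 clusters follow from the 55% versus 75% assumption; at 12 points near those rates power is about 40%

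*Protocol article*

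**What the plan says.** All the inputs stand in one paragraph of the protocol article, under *Sample size justification and power analysis*.

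- Assumed suppression at 12 months, restricted to people eligible for ART at baseline, is estimated "to be 55% in the standard-of-care arm and 75% in the intervention arm".
- Cluster size is defined by the "average cluster size (number of newly-diagnosed PLHIV per village who enroll in the study) will be 14 (range 8 to 37").
- The calculation itself opens "With a type I error rate of 0.05 (two sided"), then lists "average cluster size of 14, power of 80%, 12% difference in outcomes, and coefficient of variation of 0.24, we need 40 clusters", after allowing for 18% attrition.

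The 12% is not explained, and no second pair of rates is given for it. *Study design* confirms matched pairs of villages, two arms and 40 villages, so 20 pairs.

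**The concern.** The section gives two effect sizes for the same calculation: 20 points from the assumed rates, and 12% in the sentence that leads to 40 clusters. The required number of clusters varies roughly with the inverse square of the difference, so moving from 20 to 12 points multiplies the requirement by nearly three. The choice therefore decides whether the stated 80% power is true.

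This sentence is where a reader learns how sensitive the design is for the primary outcome. Someone who takes it at face value would expect the trial to detect a 12-point gain four times in five. If 40 clusters were derived from 20 points, the trial would more likely miss such a gain than find it.

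**Working it through.** **Inputs.** From *Sample size justification and power analysis*: two-sided alpha 0.05 (z = 1.960), power 80% (z = 0.842), k = 0.24, 14 enrolled per village, 18% attrition. From *Study design*: matched pairs, 20 pairs. Applying attrition to the cluster size gives m = 14 × 0.82 = 11.48; this is my inference, since the article does not say how attrition entered.

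**Formula.** The article names no formula. Its use of a coefficient of variation (k) with a matched-pair design points to the Hayes–Bennett form:

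V = p0(1−p0)/m + p1(1−p1)/m + k²(p0² + p1²)

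pairs = 2 + (1.960 + 0.842)² × V / (p1−p0)², with (1.960 + 0.842)² = 7.849

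power with 20 pairs = Φ( √[18 × (p1−p0)² / V] − 1.960 )

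**Step 1: reproduce the stated 40 with 55% versus 75%.**
- V = 0.0216 + 0.0163 + 0.0498 = 0.0877
- pairs = 2 + 7.849 × 0.0877 / 0.0400 = 19.21, so 20 pairs = 40 clusters, the stated number
- power = Φ(2.865 − 1.960) = 81.7%

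**Step 2: same inputs, 12 points (55% versus 67%).**
- V = 0.0216 + 0.0193 + 0.0433 = 0.0841
- pairs = 2 + 7.849 × 0.0841 / 0.0144 = 47.84, so 48 pairs = 96 clusters
- power = Φ(1.756 − 1.960) = 41.9%

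**Step 3: place the 12 points elsewhere near the stated rates.**

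| Rates | Pairs | Clusters | Power with 20 pairs |
|---|---|---|---|
| 55% vs 75% | 19.21 | 40 | 81.7% |
| 55% vs 67% | 47.84 | 96 | 41.9% |
| 59% vs 71% | 50.02 | 102 | 40.3% |
| 63% vs 75% | 52.09 | 106 | 39.0% |

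**Step 4: vary the method, holding k = 0.24 and a two-sided test.**
- Unmatched form (add 1 instead of 2), m = 11.48: 38 clusters for 55% vs 75%; 94 for 55% vs 67%, with 43.8% power.
- Attrition ignored (m = 14): power at 55% vs 67% is 45.1% with the add-on of 2, 47.1% with 1 and 49.1% with none.
- m = 14, no add-on, then clusters divided by 0.82: 15.87 / 0.82 = 19.36, again 20 per arm for 55% vs 75%; for 55% vs 67%, 41.83 / 0.82 = 51.02, so 52 per arm.
- Between-village standard deviation held at k × p0 in both arms, a more lenient model: 45.7% (add-on 2) to 47.7% (add-on 1) at 55% vs 67% after attrition. Ignoring attrition as well gives 51.6% with an add-on of 1 and 53.7% with none, the most favourable combination I tried.

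No variant brings 12 points near 80%.

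**Step 5: minimum detectable difference from 55% at 80% power with 20 per arm.** 19.5 points (matched, after attrition) down to 17.7 points (no add-on, attrition ignored), so about 18 to 20 points.

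**The case against.** **The 12% may mean something else.** Read as relative, 55% becomes 61.6%, and power after attrition is only 16% to 17%. Read as the 20 points diluted over everyone enrolled, it needs an ART-eligible share of about 60%, which the article does not give. If that share is assumed, with no suppression in the rest, the contrast is 33% versus 45% and power is 56% to 64%, depending on the add-on and on whether attrition is applied. A 12-point difference reaches 80% only if the control rate is about 14% to 20%, which is not stated for suppression. None of these readings rescues the sentence.

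**The formula is inferred.** This stands. Two different routes give 40 for 55% versus 75% (m = 11.48 with the matched add-on, or m = 14 with clusters divided by 0.82), so the text does not show which was used. The contrast between 20 and 12 points survives either route.

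**A reader might infer that the trial is underpowered and needs about 100 villages.** The article does not support that. The 40 clusters agree with the assumed rates printed in the same paragraph, so an error of reporting in one phrase is the more plausible explanation. Nor does planned power say what a null result rules out; the confidence interval does that.

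**A reader might also infer that 12 points is out of reach even without clustering.** That depends on the formula and on how attrition enters. With m = 14 and k = 0, some versions need only 20 per arm. It is also beside the point, because k = 0.24 is stated.

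**Nor is 40 × 14 = 560 against about 600 an error.** The 14 counts newly diagnosed people, while *Intervention trial* also admits known-positive people who never linked to care, and the 600 is approximate.

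**Conclusion.** The statement is wrong as written: 80% power, 40 clusters, k = 0.24 and a 12-point difference near the stated rates cannot all hold. Forty clusters match 55% versus 75% (about 82% power). At 12 points power is about 39% to 42% by the matched-pair formula after attrition, and at most about 50% across variants of that formula. Only the more lenient variance model with attrition ignored goes slightly above that.

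This rests on reading 12% as percentage points near 55% to 75%, on the stated k, and on a formula inferred from the article's own terms.

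One qualification applies to the 82% as well. The 55% and 75% are for people eligible for ART at baseline, whereas the 14 per village counts newly diagnosed enrollees, and *Setting* and *Secondary outcome measures* describe a CD4 threshold of 500 still in force when the study began. The 82% therefore treats every evaluable participant as eligible. For illustration only, an eligible share of 60% to 70% would leave 6.9 to 8.0 evaluable per village and give 71% to 75% power for 55% versus 75%.

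**What to change.** Check the original calculation and reconcile the two effect sizes.

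- If 55% versus 75% was used, replace the 12% with a difference of 20 percentage points (55% versus 75%), and add the minimum detectable difference, about 18 to 20 points from 55%.
- If 12 points is the effect of interest, keep 40 clusters and restate power as about 40% at the stated rates.

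In either case, say whether the effect and the cluster size of 14 refer to ART-eligible participants or to all enrolled, and whether the 18% attrition reduced the cluster size or inflated the number of clusters. Naming the formula would settle the second of these.

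The cost is one or two corrected sentences. Villages, enrolment and follow-up stay as planned; the published sensitivity of the design becomes less favourable than the 12% suggests.

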### Ethics

Approval of all study procedures has been obtained from the institutional review boards at San Diego State University and Makerere School of Public Health. Study approval has also been received from the Uganda National Council for Science and Technology. We will obtain written informed consent for participation in HIV testing and the brief baseline questionnaire interview. For individuals who want HIV testing, but do not want to participate in the brief questionnaire interview, verbal informed consent with a waiver for written consent will be obtained. Separate consent forms will be used to obtain written informed consent for all participants enrolled in the intervention trial or CD4 and VL Only arm.

We expect that the overall risk:benefit ratio will be favorable to patients participating in the study, and the risks related to HBHCT are not greater than the risks associated with the standard-of-care health system procedures related to home-based health services, which is commonplace in this rural Ugandan setting. Among the main risks of the study, are minimal physical risks associated with fingerstick and venous blood draws (bruising, bleeding, discomfort, lightheadedness, and potential infection), which are not greater than the risks incurred from normal medical blood testing procedures. We will minimize these risks by hiring qualified staff who also have experience in phlebotomy and finger stick blood collection to perform these procedures.

There is also the potential for breaches in confidentiality related to collected data (detailed contact information of patients, interviewer-administered computerized questionnaires, data extracted from medical records, HIV results, CD4 and VL test results). To reduce the potential for recorded data to identify the participant, we will (a) use unique identifiers (random 6 digit study identification (ID) numbers) instead of medical ID/record numbers or participant names to identify all data; (b) store of the list that links the participants’ names to their unique identifiers in a locked, secure location; (c) store participant contact details in a locked cabinet separate from the list that links participant names to study ID numbers and it will not contain the unique study ID number, (d) use encryption protocols and password protection for all data collected and/or stored electronically and encryption procedures to securely transfer data, and (e) train all study staff in the importance of and procedures for protecting participants’ confidentiality.

Participants in our study may experience discomfort while discussing sensitive information during interviewer-administered computerized questionnaires (e.g., domestic violence) and intervention counseling sessions (e.g., barriers to attending HIV care). These risks will be mitigated through clearly informing patients of their right to refuse to answer any question or engage in any discussion that makes them uncomfortable and providing adequate training to counselors and interviewers in navigating sensitive discussions. For participants receiving the intervention, the possibility of experiencing an unforeseen unintended negative consequence from participating in the intervention (e.g., negative reactions to their disclosure of HIV status). This risk will be mitigated by training counselors delivering the intervention to conduct counseling sessions only in private settings and to use judgement in which strategies are appropriate for participants based on their personal circumstances. Finally, there is potential for public disclosure of the HIV test result. However, HIV test results, like all other data, will only be identified by a randomly generated study ID number. We discuss ethical concerns and protections for participant confidentiality further in the discussion section.

## Discussion

We hypothesize that compared to individuals receiving standard-of-care, or paper-based referrals, individuals receiving the PATH/Ekkubo intervention will be more likely to be virally suppressed 12 months after HBHCT, and demonstrate shorter time to HIV care and ART initiation among those eligible. Individuals receiving the PATH intervention will receive multiple follow-up counseling sessions aimed to address barriers to HIV care. This study will indicate whether enhanced linkage to care counseling found effective in improving linkage to HIV care during facility-based HIV testing in an urban population [39] can similarly improve linkage to HIV care, and subsequently reduce VL, when integrated into HBHCT in a rural setting. This study will also provide further information on the cost-effectiveness of this approach compared to providing standard-of-care paper-based referrals during HBHCT.

The evaluation of this intervention has the ability to advance science and improve public health service delivery in several ways. To date, few randomized controlled trials have assessed interventions to improve linkage to care in the context of HBHCT, leaving a gap in our understanding of the best approaches to promote linkage to HIV care and treatment in HBHCT in SSA countries. For those in the intervention arm, it is anticipated that this study will help patients reduce barriers to accessing HIV care by providing strategies and resources to overcome stigma and other barriers, as well as the requisite knowledge, motivation, and self-efficacy needed to do so. If found effective, our study will provide information on the mechanisms through which our intervention influenced linkage behavior, which will be useful in the development of future interventions. Specifically, we will test the hypothesis based on prior research, that social support will have a protective effect against enacted and internalized stigma [32, 33, 38] and additionally test the subsequent effects on linkage to care, receipt of HIV treatment, and viral suppression. In addition, by treating the control-arm as a natural history control, our study will further contribute to the scientific literature on barriers to and facilitators of linkage to care and treatment and HIV viral suppression. This data, together with our findings on costing, have the potential to inform the integration of cost-effective avenues for follow-up and the delivery of support for HBHCT in Uganda and similar settings.

### Confidentiality and ethical considerations

Conducting a CRCT in the setting of HBHCT has unique ethical challenges surrounding confidentiality of participants’ HIV status. Given the nature of our intervention, which includes multiple home visits for PLHIV, efforts to minimize the risk of participants being identified as HIV positive in their community or families through participation in our study are paramount. In addition to commonly employed safeguards to protect participant confidentiality, such as the use of unique identifiers linked to personally identifying information and the careful storage and transfer of sensitive data (as described previously), we describe here issues of confidentiality and ethics specific to conducting research with PLHIV during HBHCT, which may also be relevant to other community-based trials that involve PLHIV, and how we’ve aimed to address them.

With research involving PLHIV, there is always small risk of public disclosure. In our study, home visits from counselors could increase risk of public disclosure. While we think it is unlikely that visits from counselors in it of itself would signal one’s HIV-positive status to others in the community, as visits from counselors and various health workers are common in Uganda for a variety of healthcare reasons (e.g., family planning, postnatal care, malaria care, immunizations), we will minimize this risk in several ways. Firstly, when counselors do home visits to HIV-positive participants for the intervention trial, they will also visit other homes nearby.

Secondly, only those who have tested HIV positive and are enrolled in the intervention trial will know that the intervention trial is about linkage to HIV care. Participants in the baseline interview and HIV testing and those who only want HIV testing will not be informed about the intervention trial and thus will not know that those who are positive and in the intervention trial will be getting home visits. The baseline assessment itself will be framed more broadly as a survey on health care access and will include questions on other health service uptake beyond HIV (e.g., family planning) to mask the study’s purpose. Masking the purpose of the study requires that we consent participants for the intervention trial after they have learned they are HIV positive.

In addition to potential breaches in confidentiality among community members, counselor visits also have the risk of family members or others overhearing discussions in which sensitive information is being addressed. Training counselors to ensure privacy during home visits, as well as training counselors to use their judgment in rescheduling a home visit if privacy is compromised will minimize this risk.

Although this risk is considered to be low, some strategies that patients elect to implement in order to engage in HIV care may potentially have unintended negative consequences on the study participant or others. To minimize this risk, counselors will be trained to respect patients’ decisions and their comfort levels with HIV care linkage strategies and goals, emphasizing the decision to engage in HIV care, disclose one’s HIV status to others, and seek social support will be a personal one of the patient. When assessing linkage behavior, all components of a patient’s physical health, mental health, and social situation will be considered when discussing linkage strategies, including the threat of domestic violence. A variety HIV care linkage strategies will be discussed with each participant to minimize the possibility that a particular plan to access care may place a patient in any danger. Participants will choose the one least likely to cause negative consequences. Counselors will screen for the threat of domestic violence when deciding on a disclosure plan and linkage strategies during the first counseling session, and will conduct a brief risk assessment for domestic violence at every subsequent meeting with participants. Should participants require additional support, counselors will refer participants to relevant staff at the clinic or hospital, who will be equipped to provide appropriate referrals as necessary to study participants for additional counseling, substance abuse issues, domestic abuse, and the threat of violence when these issues arise. Participants who disclose potential abuse (both men and women) will be immediately referred to community and/or onsite services equipped to manage situations of domestic abuse when available or to higher levels when unavailable. Immediate access to crisis intervention and emergency health services, including referrals for safe shelter, are available through the hospital as needed.

### Limitations

Among the study’s limitations is the threat for contamination between intervention and control villages. However, randomizing at the level of the village and having villages assigned to different study arms not geographically close to one another should minimize this threat. We will monitor potential contamination by asking all study participants what kind of linkage counseling they received and from whom. Interviewers conducting the follow-up assessments will be blinded to study condition, however, un-blinding is possible if participants discuss the intervention with the interviewer. We will monitor this by debriefing interviewers. In addition to individual-level data, we will collect clinic-level data; cross-classification may occur if participants seek HIV care at a clinic other than the one nearest to them. However, our data analysis approach can accommodate cross-classification. Finally, in order for participants to be eligible for participation, they must be willing to accept home visits, which may limit the generalizability of the findings. However, we judge this to be only slightly more than in any study which tracks participants via home visits, and from prior studies, we have found that very few patients decline to participate due to the possibility of being visited at home.

## Conclusion

If the PATH/Ekkubo intervention is found effective, the anticipated public health benefits include improving individual health by reducing the time in which participants are linked to care. Timely linkage to care improves treatment outcomes and reduces mortality rates [85–87]. Participation in our study in itself regardless of study condition provides individuals the opportunity to learn their HIV status, and receive diagnosis and treatment for HIV that would have otherwise gone unnoticed and untreated. Moreover, through ART’s effect on VL, increasing the number of PLHIV who are in HIV care and receiving ART will have a secondary outcome of the prevention of ongoing HIV transmission to others [48]. Our study will further add to the scientific literature on the potential population-level health benefits of behavioral interventions, by assessing population-level VL as a study outcome.

## Abbreviations

AACTG: Adult AIDS Clinical Trials Group
AIDS: Acquired Immunodeficiency Syndrome
ART: Antiretroviral therapy
ARVs: Antiretroviral medications
AUDIT: Alcohol use disorders identification test
CRCT: Cluster randomized controlled trial
HBHCT: Home-based HIV counseling and testing
HIV: Human immunodeficiency virus
ID: Identification
MOH: Ministry of health
PATH Study: Providing access to HIV care study
PLHIV: People living with HIV
SSA: Sub-Saharan Africa
TB: Tuberculosis
UVRI: Uganda Virus Research Institute
VHT: Village health team
VL: Viral load
WHO: World Health Organization
